### Design

Eligible mothers will be randomised to one of three arms: Arm 1, the control group, will receive standard practice of care during pregnancy; Arm 2 will receive the child development intervention at the first research ultrasound visit; and Arm 3 will receive the intervention at two research ultrasound visits. All mothers, infants and partners (where available) will be followed-up 6 weeks and 6 months postnatally for assessments. Participants will continue to receive routine antenatal, perinatal and postnatal care as provided by the tertiary care facility from which all participants are being recruited.

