### Intervention

Women will be randomised to one of three arms on recruitment at CHBH < 25 weeks gestation after having a fetal ultrasound examination as part of routine antenatal hospital services. The women will be blind to their arm allocation and remain blinded until study completion. Using computer-generated simple randomisation, each consecutive woman screened will be randomly allocated to a study arm. Research assistants responsible for screening will receive the study arm numbers for allocation from the study coordinator on a daily basis. The allocation sequence will be concealed from the research assistants enrolling the participants. Women recruited for Arm 1 will act as the control group and will receive one further standard US at DPHRU < 25 weeks gestation, when they will receive standard fetal growth measurements but no child development messages.

In addition to their routine antenatal US at CHBH, women recruited to Arm 2 will receive an additional US < 25 weeks gestation at DPHRU, during which they will receive messages to promote early childhood development. During the US session, the sonographer will talk with the mother and partner, if present, about the fetus’ sensory development and capacity for learning, fetal responsivity to the environment, maternal well-being and the dependence of the fetus on maternal and paternal health and well-being before and after birth.

In addition to their routine antenatal US at CHBH, women recruited to Arm 3 will receive two additional USs at DPHRU, one < 25 weeks gestation (early US) and another < 36 weeks gestation (late US). They will receive the same child development messages as mothers in Arm 2 at the first US. During the second US, in addition to childhood development messages, the sonographer will encourage the woman and her partner, if present, to personalise the baby, strengthen intentions to exclusively breastfeed, talk and sing to the child before and after birth, and counsel them on how to respond to their young infant’s emotional and learning needs.

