### Data analysis

All available data at baseline will be analysed descriptively for each intervention group and in total. Categorical data will be summarised by numbers and percentages. Continuous data will be summarised by the mean, SD and range if data are normal and by the median, IQR and range if data are skewed. Minimum and maximum values will also be presented for continuous data. Differences regarding baseline variables will be checked for clinical relevance between the three treatment groups.

A CONSORT flow diagram will be used to summarise the number of participants who were: assessed for eligibility at screening, eligible at screening, eligible and randomised, lost to or discontinued the intervention and included in the primary outcome analysis. If possible, respondents and non-respondents will be compared.

The analysis of the primary outcome will be performed on the intention-to-treat population with no imputation of missing data. In the primary analysis, child development scores will be compared to the control group. If outcome data are normally distributed, we will fit linear regression models. If not normally distributed, outcome data will be categorised and logistic regression methods will be used to assess differences between intervention and control groups. Tests will be two-sided with a significance level of 0.05, and 95% confidence Intervals will also be reported. In case of relevant differences in baseline characteristics, additional adjustment(s) for these factors will be performed within the models to address potential confounding.

A stratified analysis will be done for three pair-wise comparisons—that is, Arm 1 vs. control, Arm 2 vs. control and Arm 1 vs. Arm 2 —according to the following subgroups: partner vs. no partner accompaniment and parity.

STATA, Version 15 (StataCorp, College Station, TX, USA) will be used for all analyses. Missing data and data from those who withdraw from the study will not be interpreted.

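### The arm labels in the stratified pairwise comparisons contradict the trial's arm definitions: as written, control is compared with itself, one pair appears twice, and Arm 3 is in none

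*Protocol article*

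**What the plan says.** The protocol article fixes the arm numbers in two places.

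- Design: "Arm 1, the control group, will receive standard practice of care during pregnancy". The section then assigns the messages at a single research scan to the second arm, and for the third it states: "Arm 3 will receive the intervention at two research ultrasound visits".
- Intervention: "Women recruited for Arm 1 will act as the control group". The same section gives Arm 1 one further research scan without messages.

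The abstract describes the arms in the same way.

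The Data analysis section then says: "A stratified analysis will be done for three pair-wise comparisons". It names these as "Arm 1 vs. control, Arm 2 vs. control and Arm 1 vs. Arm 2". The strata are whether a partner accompanied the woman, and parity.

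The primary analysis, earlier in the same section, uses no arm numbers: "In the primary analysis, child development scores will be compared to the control group". Most rows of Table 2 likewise refer only to intervention and control groups.

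**The concern.** The list treats Arms 1 and 2 as the two intervention arms, next to a control group named separately. Everywhere else in the article Arm 1 is the control and the intervention arms are 2 and 3. Both numbering schemes cannot hold.

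Two things are at stake.

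- **Content.** Read with the trial's own labels, the stratified analysis has no contrast for the two-session intervention, neither against control nor against one session. The Objectives ask about messages at one or at two scans, so two of the three relevant pairs are missing from the list.
- **Labelling.** Allocation runs on arm numbers that the study coordinator passes to the screening staff. If the dataset carries those numbers, code 1 means control under the Design section but an intervention under the Data analysis section. The label Arm 2 vs control then means one session against control in one scheme and, most likely, two sessions against control in the other. A subgroup result could be reported under the wrong intervention.

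**Working it through.** **Inputs.** From Design and Intervention: Arm 1 = control, Arm 2 = one session, Arm 3 = two sessions. From Data analysis: the three listed comparisons.

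**Step 1: put control = Arm 1 into the list.**

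| Listed comparison | With the defined arm numbers | Status |
|---|---|---|
| Arm 1 vs control | Arm 1 vs Arm 1 | void |
| Arm 2 vs control | Arm 2 vs Arm 1 | valid |
| Arm 1 vs Arm 2 | Arm 1 vs Arm 2 | repeats the row above |

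**Step 2: compare with all pairs of three arms.** There are 3 × 2 / 2 = 3 distinct pairs.

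| Distinct pair | In the list? |
|---|---|
| Arm 2 vs Arm 1 | yes, twice |
| Arm 3 vs Arm 1 | no |
| Arm 3 vs Arm 2 | no |

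The list covers 1 of 3 pairs, and both missing pairs involve Arm 3.

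**Step 3: try the alternative numbering.** Suppose control was meant as a separate label, with the one-session arm called 1 and the two-session arm called 2. The list then reads one session vs control, two sessions vs control, and one vs two sessions. All three pairs are covered once. This is the only reading found under which the announced count of three makes sense, so a numbering slip is the likely cause. It still assumes that the two intervention arms kept their order when renumbered, which the article does not say.

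**Step 4: check whether any planned figure depends on the list.** Inputs from the sample size paragraph under Recruitment: difference 0.5 SD, power 90%, attrition 15%. From Data analysis: "Tests will be two-sided with a significance level of 0.05".

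- Per arm: n = 2 × (1.960 + 1.282)² / 0.5² ≈ 84.1, rounded up to 85. This matches the stated 85. A t-test calculation gives about 85.03.
- With attrition: 85 / (1 − 0.15) = 100 per arm, and 3 × 100 = 300. Both match.
- Power with 85 per arm, normal approximation: Φ(0.5 × √(85/2) − 1.960) = Φ(1.300) ≈ 90.3%.

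The calculation is for a difference between any two arms in the full sample and does not use the list. Correcting the labels changes none of these figures.

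**The case against.** The strongest reply is that this is a transparent slip in a subgroup sentence. A group cannot be compared with itself, so an analyst would notice at once, and the sentence names three entities and announces three comparisons, which points to the complete set of pairs. The Objectives and the hypothesis in the Background both cover one or two scans with messages, so a contrast of two sessions with control is clearly intended.

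Much of this stands. The slip reading is the likely one, and the sentence governs only the stratified analysis.

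A reader might infer something stronger: that Arm 3 is never analysed, or that its 100 of 300 women enter no comparison. The document does not support that. The primary analysis is by intention to treat and compares scores with the control group. Arm 3 is an intervention group by definition, and nothing in that text or in Table 2 leaves it out. Baseline description covers all three groups.

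What does not stand is the suggestion that no correction is needed. The intended contrasts can be recovered only by setting aside the arm numbers in the Design and Intervention sections, and then by assuming how the intervention arms were renumbered. The general wording of the primary analysis does not help, because it names no pairs. Nor is this a detail that an article leaves to a fuller document: the sentence is complete, and wrong as written.

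**Conclusion.** The concern holds for the list of pairwise comparisons in the stratified analysis. Under the trial's own arm definitions, one listed comparison is void, two are the same pair, and Arm 3 appears in none, which leaves one distinct pair out of three. It is the only place in the article where contrasts are named by arm number, so nothing else at that level corrects it.

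The finding is limited to that list. It does not show that Arm 3 is missing from the primary or secondary analyses, and it changes no sample size, power or significance level. It rests on one premise, that the Design and Intervention sections give the governing arm numbers; they agree with each other and with the abstract. That the cause is a numbering slip is an inference from the wording. The need for correction does not depend on it.

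**What to change.** In the Data analysis section, replace the three listed comparisons with:

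- Arm 2 vs Arm 1 (control): one message session against control;
- Arm 3 vs Arm 1 (control): two message sessions against control;
- Arm 3 vs Arm 2: two sessions against one.

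Use the arm numbers of the Design and Intervention sections, and carry the same numbers into the full protocol, any SAP and the dataset codes. Make the change before outcome data are analysed by arm, so that the contrasts cannot seem to have been chosen afterwards.

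The cost is one sentence. No data collection, participant burden or sample size is affected. How the regression models are parameterised, and whether the primary analysis uses the same pairs, are separate choices that this correction does not need to settle.

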### Procedures

#### Recruitment

Approximately 500 women present to CHBH each month for their first pregnancy US, of which 50% are < 25 weeks gestation. This offers a potential pool of 250 women per month to be included in the study. Participants will be recruited from women attending the Foetal Medicine Unit (FMU) at CHBH, where routine fetal ultrasound examinations are conducted. Eligible women will be resident within Soweto, aged 18 years and older, with a singleton pregnancy and presenting < 25 weeks gestation. Major fetal abnormalities detected during the first routine ultrasound examination conducted by an experienced radiologist in the FMU, or severe maternal morbidities, will exclude a pregnant woman from the trial. These women will be transferred to specialised clinical services at CHBH, where she will receive appropriate treatment.

Sample size calculations were based on detecting a 0.5-standard deviation (SD) difference between arms on both the Bayley III Language and Cognitive Scales, and *z*-scores for weight-for-age (WAZ), length-for-age (LAZ) and weight-for-length (WLZ) measured at 6 months of age at 90% power, which is 85 per arm. Allowing for 15% potential attrition during pregnancy and during follow-up to 6 months of infant age, the sample size in each of the three arms will be 100. This makes a total sample size of 300 women for recruitment.

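### The subgroup analysis compares arms within parity and partner strata and names no treatment-by-subgroup test, so it cannot show whether the effect differs between strata

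*Protocol article*

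**What the plan says.** The last analytic step in the Data analysis section of the protocol article is a stratified analysis of three pairwise arm comparisons, "according to the following subgroups: partner vs. no partner accompaniment and parity". The section does not say how parity is grouped or at which scan accompaniment is recorded. It gives no rule for comparing one stratum with another. The word interaction occurs in the article only for parent and infant behaviour or contact with the sonographer, never as a statistical term.

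The only inferential standard in the article stands in the paragraph before, which opens with the primary outcome: "Tests will be two-sided with a significance level of 0.05, and 95% confidence Intervals will also be reported".

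The Recruitment section sizes the trial for whole arms: "Sample size calculations were based on detecting a 0.5-standard deviation (SD) difference between arms", "at 90% power, which is 85 per arm". It then allows for 15% attrition and recruits 100 per arm.

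**The concern.** A comparison inside one stratum tests the null of no effect in that stratum. A subgroup analysis by parity or partner asks whether the effect is the same in both strata, and the stated method supplies no test or estimate of that.

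The strata are also much smaller than the arms for which 90% power was calculated. A non-significant stratum therefore says little. With a real and uniform benefit, one stratum can easily reach significance while the other does not. Such a pattern is easily reported as messages that work for first-time mothers but not for others, although nothing differs between the groups.

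**Working it through.** **Inputs from the article.** Difference 0.5 SD, 90% power, 85 evaluable per arm, 15% attrition, 100 recruited per arm (Recruitment); two-sided 0.05 (Data analysis).

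**Assumptions.** The article does not give the share of women in each stratum. I treat each factor as having two levels, with splits from 50/50 to 80/20, the same split in both arms, and a normal outcome with SD 1.

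**The plan's own figure.** n per arm = 2(1.960 + 1.282)² / 0.5² = 84.06, rounded up to 85. Then 85 / 0.85 = 100. The t-test power with 85 per arm is 90.0%. The stated figures reproduce.

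**Within-stratum power.** With m = 85 × share women per arm in a stratum, the two-sample t-test has 2m − 2 degrees of freedom and noncentrality 0.5 × √(m/2). A normal approximation for the 50/50 split gives Φ(0.5 × √(42.5/2) − 1.960) = Φ(0.345) = 63.5%; the t calculation gives 62.5%.

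**Significant in exactly one stratum.** The strata contain different women, so with powers p₁ and p₂ the probability is p₁(1 − p₂) + p₂(1 − p₁). For a uniform 0.5 SD effect:

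| Split | m per arm | Power in each stratum | Exactly one | Both | Neither |
|---|---|---|---|---|---|
| 50/50 | 42.5 / 42.5 | 62.5% / 62.5% | 46.9% | 39.0% | 14.1% |
| 60/40 | 51 / 34 | 70.6% / 52.9% | 48.8% | 37.3% | 13.9% |
| 70/30 | 59.5 / 25.5 | 77.2% / 41.7% | 54.5% | 32.2% | 13.3% |
| 80/20 | 68 / 17 | 82.5% / 29.3% | 63.5% | 24.2% | 12.4% |

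A simulation of 40,000 trials per setting, with whole numbers of women (42/43, 51/34 and 59/26 per arm), gives 47.1%, 49.2% and 54.0% for the first three rows.

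**Sensitivity, 50/50 to 70/30.**
- All 100 per arm evaluable: 42% to 51%.
- Uniform effect of 0.3 SD, 85 per arm: 40% to 42%.
- Zero effect: 2 × 0.05 × 0.95 = 9.5%, whatever the split.

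**Interaction test.** Under a uniform effect it rejects in 4.8% to 5.5% of simulated trials. Its standard error in SD units is √(2/m₁ + 2/m₂).
- 50/50: SE 0.307. Power for a 0.5 SD difference in effect is Φ(0.5/0.307 − 1.960) = 37%.
- 60/40: SE 0.313, power 36%.
- 70/30: SE 0.335, power 32%.
- At 50/50, 80% power needs a difference in effect of (1.960 + 0.842) × 0.307 = 0.86 SD.

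**The case against.** The article gives subgroups one sentence. An interaction term, an exploratory label and the layout of stratum results are ordinary content of an analysis plan, which is not shown. Nothing in the sentence excludes an interaction test, and such tests are often reported beside stratum estimates. This limits the point to the method that the article states. That method is a chosen one, and it does not answer the question a subgroup analysis asks.

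Three stronger readings are tempting, and the article does not support them.

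- **That subgroup claims will be made from stratum p-values.** The stratified sentence mentions neither tests nor claims, and the 0.05 standard belongs to the preceding paragraph. The 47% to 55% is the error rate of a side-by-side reading that the article leaves open but does not adopt. Confidence intervals by stratum, if shown, would reveal the imprecision.
- **That about half is a property of the trial.** It needs a two-level factor, an assumed split, about 85 evaluable per arm and a true effect of the full planned size. It cannot hold for all three comparisons if the two intervention arms benefit equally: their mutual comparison then has zero effect, and the figure there is 9.5%.
- **That a false subgroup result would steer the follow-on trial.** The Discussion ties the pragmatic trial to feasibility and improvement in the specified measures, and mentions no subgroup result.

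It is also fair that the interaction test has low power. That is a reason for an exploratory label. It does not make the comparison of stratum p-values valid.

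**Conclusion.** The point holds for subgroup inference and leaves the primary analysis untouched. As stated, the stratified analysis cannot show whether effects differ by parity or partner status.

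If its results are read by significance at two-sided 0.05, a uniform 0.5 SD effect with 85 per arm looks confined to one stratum in about 47% to 55% of trials, against about 5% for an interaction test. The range is per factor, per comparison and per outcome, and rests on a binary factor split between 50/50 and 70/30. A more uneven split raises it; a smaller true effect lowers it.

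**What to change.** **Parity.** State the grouping. For each arm comparison, fit one model on all women in that comparison with arm, parity and arm-by-parity. Use linear regression, or logistic regression if the outcome is categorised under the plan's rule for non-normal data. Base any statement of subgroup difference only on the interaction estimate and its 95% CI. Show stratum estimates with CIs and label the analysis exploratory.

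**Partner status.** Use the same form only if the variable is defined from information fixed before randomisation. The Intervention section randomises women at recruitment, after the routine hospital scan, and partners are then invited to the research scans. Accompaniment at those scans is therefore observed after randomisation, and Arm 3 has two such scans where the other arms have one. An interaction term does not cure that.

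**Cost.** A few sentences of analysis text and one extra model term. Parity needs no new data, since reproductive history is already collected. Partner status may have to be dropped if nothing suitable was recorded before randomisation. With about 36% power for a 0.5 SD difference in effect, few subgroup claims will be supported, and the report should say so.

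### The rule against interpreting data from women who withdraw contradicts the intention-to-treat statement and, read literally, discards valid baseline and 6-week data

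*Protocol article*

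**What the plan says.** Three statements in the Data analysis section of the protocol article bear on this point.

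- The section opens by undertaking to describe all the baseline data that are available, by group and in total.
- The primary-outcome analysis is to be "performed on the intention-to-treat population with no imputation of missing data".
- The section closes with "Missing data and data from those who withdraw from the study will not be interpreted". The term withdraw is not defined, and no outcome, visit or reason for withdrawal is exempted.

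Under Recruitment, the sample size is based on "detecting a 0.5-standard deviation (SD) difference between arms", and the number needed is given for outcomes "measured at 6 months of age at 90% power, which is 85 per arm". Losses are covered by an allowance worded "Allowing for 15% potential attrition during pregnancy and during follow-up to 6 months of infant age"; this takes the number randomised to 100 per arm.

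Data collection and Table 1 give three stages: the first research scan, 6 weeks and 6 months. Bayley III appears at 6 months only. Breastfeeding, EPDS, partner involvement, infant growth, immunisation and clinic attendance are collected at both 6 weeks and 6 months.

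**The concern.** Withdrawal happens after allocation. A population defined by randomisation cannot also leave out collected values because the woman later left. A woman seen at baseline and 6 weeks who withdraws before 6 months has valid 6-week secondary outcomes, and the closing sentence removes them. Baseline data are taken at the first research scan, which also follows randomisation, so baseline tables would likewise depend on who stayed.

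Selective loss is plausible in this design. Arm 3 has an additional research visit, and Arms 2 and 3 receive messages, images and a baby book meant to raise parental engagement. The trial's own rationale links engagement to infant development. Withdrawal could therefore be related both to arm and to outcome, which is when exclusion on a post-randomisation event does harm.

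**Working it through.** **1. The plan's own figure.** Inputs from Recruitment and Data analysis: difference 0.5 SD, two-sided alpha 0.05, power 90%, attrition 15%.

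- Per arm: n = 2(1.960 + 1.282)² / 0.5² = 2 × 10.507 / 0.25 = 84.06, rounded up to 85 (85.03 by the t-test calculation).
- Inflated: 85 / (1 − 0.15) = 100.

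Both stated figures reproduce. The 85 is the number with a 6-month outcome, so the plan already budgets for 15 of 100 women per arm (3 × 15 = 45 of 300) without one.

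**2. What the sentence removes, by type of data.**

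| Data | Seen before a later withdrawal? | Effect of the sentence, read literally |
|---|---|---|
| Baseline | Yes | Removed; conflicts with the section's opening statement |
| 6-week growth, EPDS, breastfeeding, partner involvement, immunisation, clinic attendance | Yes, if she leaves after 6 weeks | Removed |
| Bayley III, 6 months | Normally no | Nothing to remove, except a score already obtained |

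**3. Upper bound on the 6-week loss.** The documents do not split the 15% by time, or between withdrawal and loss to follow-up. If every one of the 15 per arm withdrew after the 6-week visit, the 6-week analyses would fall from 100 to 85 per arm. The standard error of an arm difference would grow by √(100/85) = 1.085, about 8.5%. For a continuous outcome with a 0.5 SD difference (an assumption at 6 weeks), power would be Φ(0.5√(100/2) − 1.960) = 94.2% with all 100 and Φ(0.5√(85/2) − 1.960) = 90.3% with 85. If all the losses came before 6 weeks, the sentence would remove no 6-week data.

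**4. Bias from missing Bayley scores, for illustration only.** Let d be the share of an arm without a score and D the mean of the missing minus the mean of the observed, in SD. Bias in the difference (intervention minus control) = d_control × D_control − d_intervention × D_intervention. All values of D and the unequal shares are assumptions.

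- 15% in both arms, same D: bias 0.
- 15% in both arms, D differing by 0.5 SD (control 0, intervention −0.5): 0.15 × 0.5 = 0.075 SD.
- 10% control, 20% intervention, D = −0.5: 0.20 × 0.5 − 0.10 × 0.5 = 0.05 SD.
- 5% control, 25% intervention, D = −1: 0.25 − 0.05 = 0.20 SD.

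These concern scores that were never observed. Replacing the closing sentence recovers none of them, so the figures are the same before and after that change and do not measure its effect. The formula also applies to observed 6-week values that are discarded, and there the change would remove the bias. The documents give no inputs for that case.

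**The case against.** The strongest reply is that the sentence adds almost nothing to the primary analysis. The intention-to-treat statement is made for the primary outcome only. Both instruments that Table 2 lists under that heading are used only at 6 months, so a woman who withdraws earlier normally has no score to lose. This stands. A reader might infer that the sentence is what turns the Bayley analysis into a completers analysis, or that it costs 0.05 to 0.075 SD of bias. The documents support neither inference: the no-imputation rule already makes the analysis available-case, and those figures rest on assumed differences among unseen scores.

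A second reply is that the wording is loose. To say that data are not interpreted could mean only that no values are inferred for these women, or it could refer to revoked consent. It is therefore not established that the investigators intend to delete observed data. But data from a woman who withdrew are observed values, so the no-imputation reading does not fit that clause, and nothing in the text limits it to revoked consent. Either way the sentence needs rewording.

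Third, it would be wrong to say that the plan ignores missing outcomes. It inflates the sample for attrition, plans contact to retain women and to learn why they leave, promises a CONSORT flow diagram, and intends to compare those who respond with those who do not if this can be done. This stands too. None of it undoes a rule that sets aside data already collected.

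Finally, imputation models and similar detail are commonly left to the SAP, which is not shown. Their absence from the article is not the point here. The point is a rule that the article does state.

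**Conclusion.** The concern holds as a wrongly stated rule. Taken literally, the closing sentence contradicts two other statements in the same section and excludes valid baseline and 6-week data, and any Bayley score already obtained, because of a post-randomisation event. Its reach is at most 15 women per arm on the plan's own attrition. This bound assumes that all attrition is withdrawal and, for the 6-week outcomes, that all of it falls after the 6-week visit. The corresponding loss of precision at 6 weeks is at most about 8.5% in the standard error, and the bias in those outcomes cannot be quantified from the documents.

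For the Bayley outcome the added effect is small, and primary power is not at issue, because 85 per arm is the number planned for. The sentence should be corrected, but it does not undermine the primary comparison.

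**What to change.** Replace the closing sentence of Data analysis with: *All randomised women are analysed in their allocated arm, and all data collected up to withdrawal are used unless consent to their use is revoked.* In the same section, describe the primary analysis as an available-case analysis of all randomised women with an observed Bayley score, under a stated missing-at-random assumption.

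Optionally, add one sensitivity analysis for missing Bayley scores that uses the baseline and 6-week data already collected. This can sit in the SAP.

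The cost is a change of wording and, if the option is taken, a little more analysis work. No new data are needed and the sample size stays at 100 per arm.
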